## Abstract

**Background:**

Childhood undernutrition remains a significant global health challenge accounting for over half of all under 5 child mortality. Moderate acute malnutrition (MAM), which leads to wasting [weight-for-length z-scores (WLZ) between − 2 and − 3], affects 33 million children under 5 globally and more than 2 million in Bangladesh alone. We have previously reported that acute malnutrition in this population is associated with gut microbiota immaturity, and in a small, 1-month pre-proof-of-concept (POC) study demonstrated that a microbiota-directed complementary food formulation (MDCF-2) was able to repair this immaturity, promote weight gain and increase plasma biomarkers and mediators of healthy growth. Here we describe the design controlled feeding study that tests whether MDCF-2 exhibits superior efficacy (ponderal growth, host biomarkers of a biological state) than a conventional Ready-to-use Supplementary Food (RUSF) in children with MAM over intervention period of 3 months.

**Methods:**

Two separate cohorts of 12–18-month-old children will be enrolled: 124 with primary MAM, and 124 with MAM after having been treated for severe acute malnutrition (post-SAM MAM). We have established several field sites in an urban slum located in the Mirpur district of Dhaka, Bangladesh and at a rural site, Kurigram in the north of Bangladesh. The two groups of children receiving MDCF-2 and RUSF will be compared at baseline (pre-intervention), after 1 month, at the end of intervention (3 months), 1 month after cessation of intervention, and every 6 months thereafter for 4 years.

**Discussion:**

This study will determine whether daily, controlled administration of MDCF-2 for 3 months provides superior improvements in weight gain, microbiota repair, and elevated levels of key plasma biomarkers/mediators of healthy growth compared to the control RUSF formulation. The pathogenesis of MAM is poorly defined and there are currently no WHO-approved treatments; results from the current study of children with primary MAM and post-SAM MAM will shed light on the effects of the gut microbiota on childhood growth/development and will provide a knowledge base that may help improve complementary feeding practices.

**Trial registration:**

The primary MAM and post-SAM MAM trials are registered in Clintrials.gov (NCT04015999 and NCT04015986, registered on July 11, 2019, retrospectively registered).

Recently, we have designed prototypes for nutritional interventions that are composed of locally available, affordable, culturally acceptable complementary foods commonly consumed in Bangladesh. Preclinical studies using gnotobiotic mice and piglets colonized with members of the gut microbiota from Bangladeshi children with acute malnutrition revealed that these formulations contain nutrients that increase the representation and expressed beneficial functions of growth-promote gut bacterial strains that are underrepresented in the microbiota of affected children [5]. Several of these microbiota-directed complementary food (MDCF) formulations were subsequently tested in a pre-POC study involving 12–18-month-old Bangladeshi children with MAM living in an urban slum (Mirpur) located in a district of the nation’s capital city [5]. This 1-month long, four-arm, controlled feeding study tested three MDCFs and a commonly used, rice-lentil-based, ready-to-use supplementary food (RUSF) that was not designed with the intention of changing gut microbial community structure or function. One of the MDCFs, MDCF-2, was distinguished from the other formulations based on its superior ability to (i) repair the microbiota of children with MAM to a configuration that resembled that of healthy individuals living in the same community, and (ii) change the levels of multiple plasma proteins involved in mediating various aspects of metabolism, bone growth, immune function and neurodevelopment towards a healthy state [5, 6]. These results support the notion that repair of impaired gut microbial community development could represent a new therapeutic concept for restoring healthy growth.

The pre-POC study involved small numbers of children (15–17/arm) and the 1-month long intervention was too brief to determine whether a substantial and durable repair of the microbiota, and the changes in the plasma proteome, would be accompanied by substantial and sustained changes in ponderal and linear growth. Here, we describe our protocols for POC trials designed to assess whether compared to RUSF, administration of MDCF-2 to larger numbers of children with MAM for longer periods of time will produce durable changes in the configurations of their gut communities, their plasma proteomes, anthropometric indicators of their growth, and their morbidities. Two cohorts of 12–18-month-old Bangladeshi children will be enrolled; one with primary MAM and the other with MAM after having been treated for severe acute malnutrition (post-SAM MAM). In each cohort, children will be randomized to one of two treatment arms; members of one arm will receive MDCF-2 while members of the control arm will receive a standard RUSF. Primary clinical outcome measures will be the rate of weight gain and the change in WLZ over the intervention period. Biospecimens (blood, feces and urine) collected before, during and after the intervention will be analysed to determine the extent of gut microbiota repair and the degree of improvement in levels of plasma biomarkers and mediators of healthy growth.

### Aim and objectives

To determine whether daily, controlled administration of MDCF-2 for 3 months provides superior improvements in weight gain, microbiota repair, and elevated levels of key plasma biomarkers/mediators of healthy growth compared to the control RUSF formulation. The sustainability of microbiota repair, growth outcomes and physiologic state will be assessed over a period of 4 years through collection and analysis of fecal and blood samples every 6 months.

## Methods

### Study design

Fig. 1 describes the designs of the two open-label, randomized control trials.

**Fig. 1 Fig1:**
[figure not shown]
Design of controlled feeding study, including time points where anthropometric data will be collected and biospecimens obtained. **a** Trial of children presenting with primary MAM. **b** Trial of children who present with SAM

Enrollment began on November, 2018 and it is expected to continue until July, 2020. Eligible participants are 12–18-month-old children of either sex with MAM (WLZ < -2 to − 3; Study 1) or SAM (WLZ < -3; Study 2). Children will be screened and enrolled through household surveys by Field Research Assistants (FRAs) following pre-specified inclusion criteria (see Table 1 for inclusion/exclusion criteria). For those who meet the enrollment criteria, a full description of the purpose of the study will be provided, including the number and type of biological samples to be collected. Parents/legal guardians who are willing to participate will provide a signed informed consent statement that is witnessed and also signed by the investigator.

**Table 1 Tab1:** inclusion/ exclusion criteria of the study participants

Inclusion	
Parent(s) willing to sign consent form; the informed consent document will explicitly request permission to use the collected fecal samples for future studies, including but not limited to culturing component bacterial strains	
Child age 12–18 months and no longer exclusively breast fed	
WLZ (<−2 to −3) without bilateral pedal edema at the time of randomization	
Parent(s) willing to bring the child to the feeding center twice daily for the first 4 weeks of nutritional therapy, once daily for the second 4 weeks, and provide feeding once daily at home for the second 4 weeks, and twice daily at home for the final 4 weeks	
Exclusion	
Medical conditions: Children with tuberculosis (diagnosis based on WHO 2014 guidelines which have been incorporated in the national TB control guidelines of Bangladesh). The guidelines depend upon the following five diagnostic principles (three out of five should be positive):	
-Specific symptoms of TB	
-Specific signs of TB	
-Chest X-ray	
-Mantoux test	
-History of contact	
Any congenital/acquired disorder affecting growth, i.e., known case of trisomy-21 or cerebral palsy; children on an exclusion diet for the treatment of persistent diarrhoea; having known history of soy, peanut or milk protein allergy	
Severe anemia (< 8 mg/dl)	
Antibiotic use within the last 15 days for Primary MAM participants	
Receiving concurrent treatment for another condition	
Failure to obtain informed written consent from parents/guardians	

Participants’ guardian/ caregiver who will provide written informed consent and participants who satisfy the inclusion/exclusion criteria will be randomized to one of the two treatment arms (MDCF-2, RUSF) using the permuted block randomization method with concealment to ensure that the allocation is not made before obtaining consent from parents/caregivers to participate in the study. A random allocation sequence will be generated using a computerized random allocation system for permuted block randomization to ensure comparable allocation number at a certain equally spaced points in the sequence of participant assignment. Parallel type of randomization will be used. Blocks of 2 and 4 will be constructed to reduce the predictability. Random assignment will be prepared in advance by an independent researcher from icddr b who has no involvement in the trial. Study staffs are blinded to random assignments.

### Sample size calculation

Primary outcome measures will include rate of weight gain, change in weight and length; change in WLZ, change in MUAC, change in LAZ, morbidity, extent of repair of gut microbial community immaturity, and changes in the levels of key plasma biomarkers of host physiological state. We plan to include 124 participants (*n* = 62/treatment arm) for the primary MAM trial and for the post-SAM MAM trial. Recruitment of 124 participants will give 80% power at 5% significance level based on the change in WLZ scores of children from the recently completed pre-POC trial of different MDCFs. In the pre-POC trial of different MDCFs, the baseline WLZ score of children who received MDCF 2 was − 2.2 and after 1 month of supplementation was − 1.7. If we consider the WLZ − 2 at baseline and − 1.7 at end line, pooled standard deviation as 0.53, then the sample size would be 49 in each arm at 80% power and 5% level of significance. With 20% attrition, 62 enrolled children will be needed for each arm in each of the two trials.

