### Data analysis plan

The two groups of children receiving MDCF-2 and RUSF in each trial will be compared at baseline and at different time points as shown Fig. 1a, b. The clinical outcome variables will include rate of weight gain, anthropometric indices, and morbidity. We will perform t-test, Mann-Whitney test, Chi-Square test and Fisher’s exact test to compare the primary clinical outcome variables between the intervention arms. Multivariable linear regression will be employed to assess the role of the nutritional interventions to the anthropometric outcome. The data analyst will be blinded to the intervention arms.

Serially collected biospecimens will be analysed for (ii) changes in the plasma proteome (characterized by quantitative aptamer-based measurements of 5000 different proteins including those that are biomarkers and mediators of bone growth, metabolism, immune function, neurodevelopment and other aspects of physiologic status), fecal, plasma and urinary metabolomes (utilizing targeted and non-targeted mass spectrometry, including the products of metabolism carbohydrate components of the diet and of host metabolic health), (iii) repair of the gut microbiota (V4-16S rDNA amplicon sequencing to identify the abundances of ecogroup bacterial taxa and qPCR assays of the levels/diversity of common enteropathogens in fecal samples) and microbiome (shotgun sequencing of fecal DNA samples to characterize changes in the representation of microbial genes including those involved in the metabolism of various nutrients). A variety of computational tools, including those that allow for feature reduction [6, 10], will be applied to these multi-omic datasets to identify significant correlations between components of the microbiota/microbiome, proteome, metabolome and clinical parameters.

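### The protocol article states its primary clinical outcomes twice and differently, while its 5% level and 80% power fit only change in WLZ as a single primary outcome

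*Protocol article*

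**What the plan says.** Four sections of the protocol article bear on this point.

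- **Background, last paragraph:** "Primary clinical outcome measures will be the rate of weight gain and the change in WLZ over the intervention period". That is two outcomes, with a time frame. Biospecimen analyses follow in a separate sentence.
- **Aim and objectives:** the question is whether MDCF-2 "provides superior improvements in weight gain, microbiota repair, and elevated levels of key plasma biomarkers/mediators of healthy growth". WLZ is not mentioned.
- **Sample size calculation, first sentence:** "Primary outcome measures will include rate of weight gain, change in weight and length; change in WLZ, change in MUAC, change in LAZ, morbidity", and after these the two biological families, "extent of repair of gut microbial community immaturity, and changes in the levels of key plasma biomarkers of host physiological state". That is seven clinical outcomes plus two biological families, with no ranking and no time point. The same paragraph then sizes each trial on change in WLZ alone, at 80% power and a 5% significance level.
- **Data analysis plan:** "The clinical outcome variables will include rate of weight gain, anthropometric indices, and morbidity". The t-test, Mann-Whitney, chi-square and Fisher tests will be used "to compare the primary clinical outcome variables between the intervention arms", but the section does not say which variables those are. It also plans "quantitative aptamer-based measurements of 5000 different proteins"; no section says which of these count as key.

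**The concern.** The two lists cannot both be right. Change in weight, length, MUAC, LAZ and morbidity are all clinical. All five are primary in the Sample size calculation section and absent from the Background's list. The Data analysis plan could have settled the matter but refers to the primary clinical variables without naming them.

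The sizing makes this more than an untidy list. A calculation that gives the full 5% to one outcome presumes that one outcome decides the trial, yet the sentence opening that section calls nine things primary. The aim is to show superiority, and nothing in the article says which comparison would establish it. If that stays open until results are known, the success criterion can be chosen from several candidates, and the stated error rate and power describe only one of them.

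**Working it through.** **Inputs.** From Sample size calculation: WLZ difference 0.3 (from −2 to −1.7), SD 0.53, power 80%, level 5%, 20% attrition, 49 evaluable and 62 enrolled per arm. Sidedness is not stated. From the outcome lists: 2 primary clinical outcomes in the Background; 7 clinical plus 2 biological families, 9 in all, in Sample size calculation.

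**Step 1: reproduce the plan's figure.** With the two-sided normal formula,

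n per arm = 2 × [SD × (z₀.₉₇₅ + z₀.₈₀) / difference]² = 2 × [0.53 × (1.960 + 0.842) / 0.3]² = 48.99, so 49.

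Enrolled: 49 / (1 − 0.20) = 61.25, so 62. Both figures reproduce. A one-sided 5% would give 39, so the plan used an undivided two-sided 5% for WLZ.

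**Step 2: false-positive chance if any listed primary could carry the claim at 5%.** For k independent outcomes it is 1 − 0.95ᵏ:

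- k = 2: 1 − 0.95² = 9.75%
- k = 9: 1 − 0.95⁹ = 37.0%

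The article gives no correlations, so a common correlation was assumed and k equicorrelated normal statistics were simulated (400,000 draws, two-sided 5% each, each biological family counted as one test):

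| Assumed correlation | 2 outcomes | 9 outcomes |
|---|---|---|
| 0 | 9.8% | 37.0% |
| 0.3 | 9.5% | 32.6% |
| 0.5 | 9.1% | 26.9% |
| 0.7 | 8.4% | 20.3% |
| 0.9 | 7.0% | 12.3% |

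These figures are per trial and count one time point per outcome.

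**Step 3: cost of splitting alpha.** With 49 per arm, the standard error of the difference is 0.53 × √(2/49) = 0.107, and 0.3 / 0.107 = 2.80. Power is Φ(2.80 − z), where z is the two-sided critical value.

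| Rule | Level per outcome | z | Power for WLZ at 49 per arm | Evaluable / enrolled per arm for 80% |
|---|---|---|---|---|
| WLZ alone | 0.05 | 1.960 | 80% | 49 / 62 |
| Two primaries, Bonferroni | 0.025 | 2.241 | 71% | 60 / 75 |
| Nine primaries, Bonferroni | 0.0056 | 2.773 | 51% | 82 / 103 |

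Only the first row matches the enrolment that the article states.

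**The case against.** Much can be said for the plan.

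- **The 5% level is tied only to WLZ.** A reader might infer that all nine outcomes are each tested at 5% and that any one success suffices. The article does not say so. The inference rests on 5% being the only level given, and the error rates in step 2 are conditional on it.
- **The Background speaks of clinical outcomes.** Microbiota repair and plasma biomarkers therefore do not contradict it. The direct conflict is confined to five clinical items, one of which, change in weight, largely duplicates rate of weight gain.
- **Independence is untenable.** Rate of weight gain, change in weight and change in WLZ share the same body weight, and change in length and LAZ share the same length. The 37% is an upper end, not a best estimate.
- **No protein-by-protein test at 5% is described.** A reader might infer that every assayed protein would be compared between arms at 5%, with a large crop of chance findings. The article makes only key biomarkers primary and describes computational tools with feature reduction, used to find correlations across the omics and clinical data. That inference is not supported.
- **This is a condensed article on proof-of-concept trials.** A multiplicity rule or a list of key proteins may stand in a fuller document. It would be wrong to say that the error rate is uncontrolled; the article simply states no control.

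All of this stands, and it limits the point. It does not remove the conflict: the article states its primary clinical outcomes twice, differently, and sizes each trial for one outcome. A later multiplicity rule that splits alpha would leave the stated 80% untrue at 49 evaluable per arm.

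**Conclusion.** The point holds in this form: the Background and Sample size calculation sections conflict on the primary clinical outcomes (two against seven), the Data analysis plan does not resolve the conflict, and no section says which result decides superiority. The sample size arithmetic is correct, but its 5% level and 80% power are true of the trial's conclusion only if change in WLZ is the single primary outcome.

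The size is conditional. If any listed primary could carry the claim at 5%, the chance of at least one false positive per trial is about 12% to 37% for the nine and about 7% to 10% for the Background's two. Both ranges rest on assumed common correlations from 0.9 down to 0, and every value exceeds 5%. The power losses in step 3 rest on the plan's own difference and SD and on Bonferroni splitting.

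**What to change.** Before unblinding, make the Background, Aim and objectives, Sample size calculation and Data analysis plan sections agree.

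- **Preferred:** name one primary outcome for each trial, change in WLZ from baseline to the end of the 3-month intervention. It is the outcome that was sized, so 62 per arm stands, and the stated level and power apply to the deciding test. Make rate of weight gain the first secondary outcome, and the remaining outcomes secondary or exploratory.
- **Acceptable alternative:** keep the Background's two primaries, state the alpha rule, and restate power for WLZ as about 71% at 0.025 each with 49 evaluable per arm.
- **In either case:** have the Data analysis plan name the variables it tests as primary, and fix the list of key proteins before treatment codes are seen.

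The change is one of wording and needs no further enrolment. Its price is that the sponsor can no longer call the other outcomes primary or, under the alternative, must state a lower power.

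### The stated 80% power is not shown to apply to the between-arm comparison of 3-month WLZ change: the SD of 0.53 is not identified as an SD of change, and the planning values come from a 1-month pilot

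*Protocol article*

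**What the plan says.** The Sample size calculation section of the protocol article bases the 80% power on WLZ change in the pre-POC pilot. It reports that the pilot's MDCF-2 children started at a mean of −2.2 and that the value "after 1 month of supplementation was − 1.7". It then adopts slightly different planning values, "WLZ − 2 at baseline and − 1.7 at end line, pooled standard deviation as 0.53", and concludes that the "sample size would be 49 in each arm at 80% power and 5% level of significance". Allowing for 20% attrition gives 62 enrolled per arm, and this number serves both the primary MAM trial and the post-SAM MAM trial.

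The Background states: "Primary clinical outcome measures will be the rate of weight gain and the change in WLZ over the intervention period". The Abstract and the Aim and objectives section set that period at 3 months, and the Data analysis plan compares outcomes between the two arms. The Sample size section lists further primary outcomes, but WLZ is the only one for which a calculation is given. The Background also says of the pilot that "the 1-month long intervention was too brief to determine" whether substantial, lasting growth changes would accompany the biological ones.

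**The concern.** A power figure belongs to one comparison: a given difference, in a given variable, with that variable's SD. Here the comparison is the between-arm difference in individual WLZ change over 3 months. The calculation instead gives two WLZ levels, one at baseline and one at end line, and a pooled SD. The text does not say what was pooled, or whether 0.53 describes levels or changes. These differ: the SD of change depends on how strongly a child's two values are correlated, and it may differ between 1 and 3 months.

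The time horizon is a second gap. The pilot values quoted cover 1 month, and no 3-month value enters the calculation. Nor does any value from post-SAM children, who come to randomization after SAM treatment and from two sites, whereas the pilot enrolled children with MAM in Mirpur.

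At stake is how the result is read. A null 3-month finding would be taken to come from a trial with 80% power, when that figure was not derived for the 3-month between-arm comparison.

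**Working it through.** **Inputs from the protocol article (Sample size calculation):** difference 0.3 (−2 to −1.7), SD 0.53, 5% significance, 80% power, 20% attrition. Sidedness is not stated; two-sided reproduces the figure.

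**Step 1. Reproduce the plan's figure.**
n per arm = 2 × (z for 5% two-sided + z for 80%)² × SD² / difference² = 2 × (1.960 + 0.842)² × 0.53² / 0.3² = 48.99 with unrounded quantiles, hence 49. Then 49 / 0.8 = 61.25, hence 62. Power at 49 per arm is 80.0% by the normal formula and 79.2% by the t-test. A one-sided test would give 39, and a paired one-sample formula 25. So 0.53 was entered in the two-independent-sample formula as the SD of the outcome compared.

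**Step 2. Suppose 0.53 is the SD of WLZ levels, equal at both visits (assumption).**
SD of change = 0.53 × √(2(1 − ρ)), where ρ is the within-child correlation, which the article does not give. The difference is held at 0.3, with 49 per arm and a two-sided t-test; n needed is from the normal formula.

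| ρ | SD of change | Power at 49 per arm | n per arm for 80% |
|---|---|---|---|
| 0.3 | 0.627 | 65% | 69 |
| 0.4 | 0.581 | 72% | 59 |
| 0.5 | 0.530 | 79% | 49 |
| 0.6 | 0.474 | 87% | 40 |
| 0.7 | 0.411 | 95% | 30 |
| 0.8 | 0.335 | 99% | 20 |

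The stated power is matched only at ρ = 0.5.

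**Step 3. Suppose instead that 0.53 is already an SD of change, but over 1 month.**
The 3-month SD is not given; the values below are assumed. The smallest difference detectable with 80% power at 49 per arm is 0.572 × SD (t-test).

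| 3-month SD of change (assumed) | Power for 0.3 | Detectable difference |
|---|---|---|
| 0.53 | 79% | 0.30 |
| 0.60 | 69% | 0.34 |
| 0.65 | 62% | 0.37 |
| 0.70 | 56% | 0.40 |
| 0.80 | 45% | 0.46 |

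These assumed SDs, apart from the reference row, all exceed 0.53, so this table can only show lower power. The between-arm effect could also be larger at 3 months.

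**Step 4. What the 0.3 stands for.**
It is a baseline-to-end-line change. It equals a between-arm difference only if children on RUSF do not change at all, and the section gives no RUSF value. With SD 0.53 and 49 per arm, an assumed between-arm difference of 0.20 has 46% power and 0.15 has 28% (t-test). Correcting the SD while keeping 0.3 would therefore leave this second problem in place.

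**The case against.** The strongest reply is that nothing here is miscalculated. The 49 and the 62 reproduce exactly, a journal article may leave the derivation of an SD to the full protocol, and the section does say that the power rests on change in WLZ. On that reading 0.53 could be an SD of change pooled across arms. This stands in part: there is no arithmetic error, and the meaning of 0.53 is open. It does not settle the point, because the pilot values quoted cover 1 month on any reading, and the article publishes a complete calculation that readers will rely on.

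A reader might go further and infer that 0.53 has to be an average of a small entry SD and a much larger end-line SD. The entry rule, "WLZ (<−2 to −3) without bilateral pedal edema at the time of randomization", spans one z-unit, so an entry SD cannot exceed 0.50; with the pilot's mean of −2.2 in the same window it cannot exceed √(0.2 × 0.8) = 0.40. The documents do not support that inference. It presupposes that 0.53 describes levels at two visits. It also applies this trial's entry window to the pilot, whose criteria are not given; the Background's definition of MAM also admits children on MUAC. Even if it is granted, with entry SDs of 0.20 to 0.40, power at 49 per arm runs from 57% to 90% for correlations of 0.3 to 0.7, and reaches 96% at 0.8 with entry SD 0.40. That range includes 80%.

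The Background's remark on the pilot should not be stretched either. It concerns whether substantial and sustained growth effects could be seen, not whether an SD could be estimated.

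**Conclusion.** The point holds in a limited form. The 80% is not shown to be the power of the between-arm comparison of 3-month WLZ change, the only one of several primary outcomes that is powered. The SD is not identified as the SD of individual change, the pilot evidence covers 1 month, and the same inputs are carried to the post-SAM trial.

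A reader might infer that the trials are underpowered. That is not established. For a 0.3 difference, power is about 65% to 95% for correlations of 0.3 to 0.7 if 0.53 is the SD of levels at both visits, and 69% to 45% if the 3-month SD of change is 0.60 to 0.80. The correlations and the 3-month SDs are assumptions, and all these figures hold 0.3 fixed as the between-arm difference, which the article does not justify. This should be corrected because the figure will shape how a null result is read; it does not call the trial's conduct or analysis into question.

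**What to change.** Restate the power for the comparison actually planned, separately for the primary MAM and post-SAM MAM trials:

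- Replace 0.53 with the SD of individual WLZ change over 3 months, estimated from blinded data with both arms combined. If only the pilot is used, take the SD of paired 1-month changes and label the result as 1-month power.
- Report the smallest between-arm difference in 3-month change detectable with 80% power at 49 completers per arm, about 0.57 × that SD.
- Give any restated power for an explicitly assumed MDCF-2 versus RUSF difference in 3-month change, with its source, and not for the baseline-to-end-line change of 0.3.

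The cost is a short recalculation and revised wording. Enrolment, visits and procedures stay as they are. The restated figure may be less favourable than 80%.

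### The sample size enters a before-to-after WLZ change as if it were the MDCF-2 minus RUSF difference, so the 80% power is conditional on a between-arm difference of 0.30 that the protocol does not justify

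*Protocol article*

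**What the plan says.** All the planning inputs stand in the protocol article, Methods, Sample size calculation. The power claim is "Recruitment of 124 participants will give 80% power at 5% significance level based on the change in WLZ scores of children", with the pre-POC trial as its source. The pilot figures quoted are for one arm only: "the baseline WLZ score of children who received MDCF 2 was − 2.2 and after 1 month of supplementation was − 1.7". The planning values follow: "If we consider the WLZ − 2 at baseline and − 1.7 at end line", and then "pooled standard deviation as 0.53, then the sample size would be 49 in each arm at 80% power and 5% level of significance". Allowing 20% attrition, this becomes 62 per arm and 124 per trial, and the same number is used for the primary MAM and the post-SAM MAM trial.

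The comparison the trials are built for is between arms. The Background says that "members of one arm will receive MDCF-2 while members of the control arm will receive a standard RUSF". The Aim is superiority over RUSF after 3 months, and the Data analysis plan compares outcomes between the two arms. The Background also describes the pilot: "This 1-month long, four-arm, controlled feeding study tested three MDCFs" together with an RUSF. A concurrent RUSF change therefore existed, but none is quoted.

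**The concern.** Both planning values are labelled as time points (before and after), not as arms. Their difference is a change within children. A two-group sample size needs the difference in mean change between MDCF-2 and RUSF. The two quantities coincide only if the RUSF arm does not change at all, and the protocol gives no reason to expect that of an active supplement served in the same 25 g portions.

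What is at stake is the meaning of the 80%. It is the only justification of size given for either trial. As written, a reader cannot tell what MDCF-2 versus RUSF difference the trials can detect, or whether the pilot made that difference plausible. That matters most if a trial ends without a significant difference.

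**Working it through.** **Inputs** (all from Sample size calculation): difference 0.30 (−1.7 minus −2); SD 0.53; significance level 5%; power 80%; attrition 20%. Whether the test is one- or two-sided is not stated.

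**Step 1: reproduce the stated size.**

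- Two independent groups, two-sided: n per arm = 2 × (1.960 + 0.842)² × (0.53/0.30)² = 48.99, rounded up to 49. This matches.
- Attrition: 49/0.8 = 61.25, rounded up to 62 per arm, so 124 per trial. This matches.

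**Step 2: rule out other readings.**

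- Single-group before/after formula: (1.960 + 0.842)² × (0.53/0.30)² = 24.5, so 25.
- Two groups, one-sided: 39 per arm.
- Two groups, two-sided, with the pilot's full change of 0.5: 18 per arm.
- Two groups, two-sided, t-based: 49.97, so 50 per arm.

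Of these, only the two-sided two-group normal formula with 0.30 gives 49. The before-to-after change was therefore entered as the between-arm difference.

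**Step 3: power by true between-arm difference.** Two-sided t-test, 49 evaluable per arm. The SD of change is taken as 0.53, which is an assumption because the text does not say what the 0.53 measures.

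| Between-arm difference in WLZ change | Power |
|---|---|
| 0.40 | 96% |
| 0.30 | 79% |
| 0.25 | 64% |
| 0.20 | 46% |
| 0.15 | 28% |
| 0.10 | 15% |

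**Step 4: what this means for the RUSF arm.** The protocol gives no RUSF change, so the RUSF gains below are assumed.

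| Assumed RUSF gain | Power if MDCF-2 gains 0.30 (planning value) | Power if MDCF-2 gains 0.50 (pilot value) |
|---|---|---|
| 0 | 79% | above 99% |
| 0.10 | 46% | 96% |
| 0.20 | 15% | 79% |

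The same RUSF gain of 0.10 leaves either 46% or 96%, depending on which MDCF-2 gain is used.

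**Step 5: sensitivity to the SD.** If 0.53 is the SD of WLZ at one time point, the SD of change is 0.53 × √(2(1 − ρ)), where ρ is the correlation between the two measurements. For assumed ρ of 0.3, 0.5 and 0.7 this is 0.63, 0.53 and 0.41. Power for a true difference of 0.30 is then 65%, 79% and 95%.

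**Step 6: how much the pilot contrast can say.** The Background gives 15–17 children per pilot arm. With 16 per arm and SD 0.53, the standard error of a difference is 0.53 × √(2/16) = 0.187. The 95% interval is about ±1.96 × 0.187 = ±0.37, wider than the 0.30 in question.

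**The case against.** The strongest reply is that power depends only on the between-arm difference, and 0.30 may be a reasonable one. The pilot MDCF-2 gain was 0.5 in one month, so planning on 0.30 is cautious relative to that, and an RUSF gain of 0.2 would leave exactly 0.30. This stands as a limit on the conclusion. It does not rescue the derivation: the protocol does not present 0.30 as 0.5 less an RUSF gain but names it a baseline and an end-line value.

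A reader might infer that true power is far below 80%. The documents do not support that. It follows only if the MDCF-2 gain is held at 0.30 while RUSF gains something; with the pilot's gain, power can equally be above 80%. The SD could also move it either way.

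A reader might also count other oddities as errors in the size. A planning baseline of −2 sits at the edge of an entry criterion that requires WLZ below −2, but only the difference of 0.30 enters the formula, so n is unaffected. Choosing 0.3 rather than 0.5 is an explicit planning assumption and increases n. Nor can one say that the pilot was confined to primary MAM: the Background says only that the children had MAM.

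**Conclusion.** The point holds as an error in the design assumption, not in the arithmetic; 49 and 62 both reproduce exactly. A within-child change was used where a between-arm difference is required. Under the plan's own inputs (MDCF-2 gain 0.30, SD 0.53), about 80% power holds only if RUSF children gain nothing. More generally it requires a true MDCF-2 minus RUSF difference of 0.30 in WLZ change, for which the protocol offers no evidence. If the true difference were 0.20, power would be 46%; if 0.40, 96%.

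These figures rest on 49 evaluable children per arm, a two-sided 5% t-test and an SD of change of 0.53. Applying pilot figures from one month in children with MAM to a 3-month endpoint, and to the post-SAM MAM trial, is a further assumption that the protocol does not state as such. The direction of any shortfall or surplus in power cannot be settled from the document.

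**What to change.** Keep the numbers enrolled and rewrite the paragraph:

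1. Replace the −2 to −1.7 derivation with a statement of this kind: with 49 evaluable per arm (62 randomised), each trial has about 80% power (79% by t-test) to detect a between-arm difference of 0.30 in WLZ change from baseline to 3 months, two-sided 5%, if the SD of change is 0.53.
2. Say whether 0.53 is the SD of change; if it is not, give the SD of change.
3. Report the pre-POC MDCF-2 minus RUSF difference in WLZ change with its SD and confidence interval, noting the 15–17 children per arm. It is context for the 0.30, not proof of it.
4. Tabulate power for differences from 0.10 to 0.40.
5. State that using one-month MAM pilot figures for a 3-month endpoint and for the post-SAM MAM trial is an assumption.

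The cost is one paragraph and one small table. No extra children are needed and the analysis does not change. The downside is that the stated power becomes conditional and may look less favourable.
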